### Trial design {8}

This study employs an exploratory sequential mixed-methods design [53] comprising three separate phases. The phase one focuses on the cultural and methodological adaptation of the DeprEnd EMDR therapy protocol using qualitative exploratory methods, including expert consultations and thematic analysis. This phase has been previously published in a dedicated peer-reviewed article [54] and here it is summarized only to provide continuity for phases two and three. The phase two consists of a quantitative pilot feasibility study by using a single-group pre- and post-test design [55] to assess feasibility, acceptability, safety, and preliminary symptom change following delivery of the adapted intervention. Finally, phase three comprises a multi-center, two-arm, single-blind randomized controlled trial designed to compare in-person mode with online by using a non-inferiority framework. Randomization, blinding, and hypothesis testing apply exclusively to phase three, whereas phase two is intended for feasibility assessment and intervention refinement.

## Methods: participants, interventions, and outcomes

### Study setting {9}

The present study will be conducted across multiple settings corresponding to the sequential three phases of the research.i.Phase one will be conducted through a narrative literature review, expert consultations (involving EMDR therapists) based in Pakistan. These activities will be carried out through a combination of in-person meetings and secure online platforms, depending on participant availability.ii.Phase two will be implemented in both online and in-person clinical settings at the selected clinics or psychotherapy centers located in the three selected cities in Pakistan, where the adapted DeprEnd EMDR therapy protocol will be delivered by four EMDR certified therapists. Data collection during this phase will occur through clinical assessments and standardized self-report measures.iii.Finally, phase three will be conducted as a multi-center randomized controlled trial study implemented in both online and in-person clinical settings at the selected clinics or psychotherapy centers located in the three selected cities in Pakistan, where the adapted DeprEnd EMDR therapy protocol will be delivered by four EMDR certified therapists. Data collection during this phase will occur through clinical assessments and standardized self-report measures. During this phase, process fidelity and adherence to the adapted DeprEnd EMDR protocol will be monitored at mid of therapy. 

#### Research framework of study

Figure 2 illustrates a three-phase horizontal flow diagram. Phase one (Exploratory Qualitative Phase) presents the adaptation of the DeprEnd EMDR therapy protocol and preparation/readiness activities. This phase has been published in detail elsewhere [54].

**Fig. 2 Fig2:**
[figure not shown]
Research framework of study

Phase two (Quantitative Experimental Pilot Phase) shows the pilot testing process among a sample of *n* = 25. It includes baseline (T01), mid-treatment (T02), and end-of-treatment (T03) assessments, capturing dimensions of feasibility, acceptability, symptom measures, and client satisfaction. Phase three (Final Experimental Trial) includes a sample of *n* = 80 selection and allocation, repeated assessments (T01, T02, and T03), and ends with the outcomes box, summarizing the study’s outcomes such as clinical effectiveness, process quality, implementation outcomes, and symptom trajectories. Arrows between phases of the study highlight the sequential progression in the study from protocol development through pilot testing to full trial evaluation.

### Clients selection and sample size {14}

The study focuses on individuals with MDD in Pakistan, specifically selecting geographically accessible participants residing in the major cities of Rawalpindi, Islamabad, and Peshawar. Recent literature cites various studies such as by Ishtiaq et al. [56], Noor et al. [57] and Umar et al. [58] on the high prevalence of depressive disorders in these three cities of Pakistan. However, since the exact number of MDD cases in these three major cities is unknown, a more customized, multi-stage sampling procedure has been adopted.

Initially, three rehabilitation centers located in the selected cities will be randomly but purposively picked for recruiting patients. The centers will not be chosen fully at random; rather, the characteristics of the vicinity and patient flow into centers will be considered. Within each selected center, clients will be recruited using a sequential consecutive sampling technique with a rolling enrollment strategy. This approach involves selecting every eligible patient who meets the inclusion criteria until the required sample size is achieved [59]. The estimated sample size of (*n* = 80) was calculated by using the below given approximation method for two independent group means, as recommended in the existing literature by Sakpal [60] and Chow [61]:$$n=\frac{\left({Z}_{\frac{\alpha }{2}}+{Z}_{\beta }{)}^{2}\cdot (2{\sigma }^{2}\right)}{\left({M}_{1}-{M}_{2}{)}^{2}\right.}$$where.

*n*= is the estimated sample size.

Zα/2 = is the Z-score matching to the desired α level (for e.g., 1.96 for 95% confidence).

Z*β* = is the Z-score matching the desired power level (for e.g., 0.84 for 80% power).

σ^2^ = is the pooled variance of two groups.

µ​_1_ - µ​_2_= are the expected difference in means of depression scores.

A two-sided significance level of α = 0.05 was selected, consistent with conventional recommendations for clinical trials, resulting in α/2 = 0.025 and a corresponding Z-score of 1.96. Statistical power was set at 80% (1 − β = 0.80), yielding β = 0.20 and a corresponding Z-score of 0.84.

Based on previously published depression trials utilizing the Hamilton Depression Rating Scale-17 [62], a pooled standard deviation (σ = 8 points, variance = 64) for change scores was assumed. An expected mean difference of five points of the scale between the two treatment groups was specified, representing a clinically meaningful difference in depressive symptom severity. Substituting these values into the formula:$$n=\frac{\left(1.96+0.84{)}^{2}\times (2\times {8}^{2}\right)}{{5}^{2}}$$$$n=\frac{7.84\times 128}{25}$$$$n=40$$

Hence, the estimated sample size required was 40 clients per treatment arm, resulting in a total sample size of 80 clients. Furthermore, to account for potential attrition, a dropout rate of 15% was assumed, consistent with longitudinal psychotherapy trials. The adjusted recruitment target was calculated using the formula:$${n}_{\mathrm{initial}}=\frac{{n}_{\mathrm{target}}}{1-r}$$$${n}_{\mathrm{initial}}=\frac{80}{0.85}=94$$

Accordingly, approximately 94 clients will be recruited to ensure that at least 80 participants complete the trial and are available for primary analysis.

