## Statistical methods

### Statistical methods for primary and secondary outcomes {20a}

All quantitative analyses in Phase two and Phase three will be conducted using appropriate statistical methods aligned with the study design, outcome structure, and hypotheses. Analyses will be performed using standard statistical software (e.g., SPSS and Python 3.10+, standard statistical libraries). Phase two analyses will focus on feasibility, acceptability, safety, and preliminary symptoms change following delivery of the culturally adapted DeprEnd EMDR protocol. Feasibility indicators will be summarized using descriptive statistics, and a one-sample t-test with 95% confidence intervals and significance levels. Repeated-measures General Linear Models will be used to determine temporal symptoms changes. These analyses will be exploratory and will not be intended to establish definitive clinical effectiveness.

Phase three analyses will be conducted within a randomized controlled trial framework. First, non-inferiority is evaluated by comparing the estimated 95% confidence interval for the between-group difference to a pre-specified margin; if the upper bound lies entirely below the margin, non-inferiority is concluded [81]. For the primary outcome, non-inferiority is based on the between-group difference in change scores on the Hamilton Depression Rating Scale-17 from baseline (T1) to the end of treatment (T3), calculated as online EMDR minus in-person EMDR. A non-inferiority margin (δ) of 3 points was pre-specified a priori, consistent with previously published non-inferiority trials that defined margins on this scale [82]. For secondary outcomes of anxiety, as assessed by the Generalized Anxiety Disorder-7, between-group differences in change scores will be examined using analogous comparative principles and reported with effect estimates and confidence intervals. A non-inferiority margin (δ) of approximately 2.5 points on this scale was pre-specified a priori, informed by clinically meaningful score differences used in prior non-inferiority psychotherapy trials [83].

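### The 40 per arm comes from a superiority calculation on 5 points, but the primary test is non-inferiority at 3 points: power is about 39%, not 80%, if the arms are truly equal and the SD is 8

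*Protocol article*

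**What the plan says.** In the protocol article, Trial design {8} sets phase three up to "compare in-person mode with online by using a non-inferiority framework". Hypothesis ii, the comparator section {6b} and the primary outcome {12} agree: the question is whether online delivery is non-inferior to in-person delivery on HAM-D-17 change from baseline to end of treatment.

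Statistical methods {20a} gives the decision rule. The difference is online minus in-person, the 95% confidence interval is compared with the margin, and non-inferiority is concluded if the upper limit lies below it. "A non-inferiority margin (δ) of 3 points was pre-specified a priori".

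The sample-size section {14} uses other terms. "A two-sided significance level of α = 0.05 was selected", power is set at 80%, and "a pooled standard deviation (σ = 8 points, variance = 64) for change scores was assumed". Then: "An expected mean difference of five points of the scale between the two treatment groups was specified". The conclusion is that "the estimated sample size required was 40 clients per treatment arm, resulting in a total sample size of 80 clients", raised to about 94 recruits for 15% dropout. No other power statement covers the non-inferiority test.

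**The concern.** A superiority formula and a non-inferiority formula look alike, but their denominators differ. For superiority it is the square of the difference to be detected, here 5 squared. For non-inferiority it is the square of the margin minus the assumed true difference, here 3 squared if the modes are equal. The protocol uses the first to justify a trial whose primary conclusion rests on the second.

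The 5-point figure also fits badly with the aim. If it means online is 5 points worse, non-inferiority at 3 points is false. If it means online is 5 points better, the design presumes a superiority that the hypotheses do not claim.

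At stake is how the result is read. Readers are told that the trial has 80% power. If it does not, the most likely result with truly equal modes is an interval that crosses the margin, and a reader who trusts the stated power could take that as evidence against online delivery. The futility rule in the second interim analysis also depends on the chance of showing non-inferiority, which would be low from the start.

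**Working it through.** **Inputs**
- Two-sided alpha 0.05 (z = 1.96), power 80% (z = 0.84), SD of change 8, difference 5, 40 per arm, 15% dropout: sample-size section {14}.
- Margin 3, upper limit of the 95% interval (one-sided 0.025): Statistical methods {20a}.
- True difference 0 for the non-inferiority test: an assumption, since the protocol states none. It is the conventional one and is varied below.

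**1. The protocol's own figure**

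n = (1.96 + 0.84)² × 2 × 8² / 5² = 7.84 × 128 / 25 = 40.1 per arm. With 40 per arm, superiority power at 5 points is 79.8%. Recruitment: 80 / 0.85 = 94.1. The printed arithmetic reproduces.

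**2. Precision at 40 per arm**

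SE = 8 × √(2/40) = 1.789. Half-width = 1.96 × 1.789 = 3.51 (3.56 with the t distribution). To pass, the observed difference must be below 3 − 3.51 = −0.51, so online must be observed more than half a point better. An observed tie fails if the observed SD is near 8.

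**3. Power of the stated rule**

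Power = Φ(3/1.789 − 1.96) = Φ(1.677 − 1.96) = 38.9% (38.1% with t).

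**4. Sample size for 80% power under the stated rule**

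n = 7.84 × 128 / 3² = 111.5, so 112 analysed per arm, 224 in total. Allowing for dropout, 224 / 0.85 = 263.5, so 264 recruited.

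**5. Sensitivity** (SD 8, true difference 0 and 40 per arm unless stated)

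| Variation | Non-inferiority power |
|---|---|
| Online truly 1 point worse | 20.0% |
| Online truly 1 point better | 60.9% |
| Online truly 2 points better | 79.8% |
| All 94 recruits analysed (47 per arm) | 44.4% |
| 34 per arm | 34.0% |
| One-sided 0.05 (not the stated rule) | 51.3% |
| SD 7 | 48.3% |
| SD 6 | 60.9% |

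The 34-per-arm row applies if enrolment stops at 80, as Recruitment {15} says, and 15% then drop out: 80 × 0.85 / 2 = 34. The sample-size section instead recruits 94.

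With 40 per arm, 80% power needs a margin of about 2.80 × 1.789 = 5.0 points, or an SD of about 3 / (2.80 × √(2/40)) = 4.8.

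**6. The 5 points taken literally**

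If online were truly 5 points worse, the chance of passing is Φ((3 − 5)/1.789 − 1.96) = Φ(−3.08), about 0.1%.

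**The case against.** The 39% is conditional. The protocol gives no true difference for the non-inferiority test, and power rises to 60.9% if online is 1 point better. The SD of 8 rests on a cited source that cannot be checked here. With a smaller observed SD, below about 6.7 (3 / (1.99 × √(2/40))), an observed tie would pass. The 5 points can also be read as a loosely worded detectable difference, since the protocol calls it clinically meaningful and the formula carries no sign. Nothing in the protocol says that failing the rule would be taken as inferiority. And the arithmetic as printed is correct.

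Most of this is fair as to wording. The figure must carry its conditions, the conflict between a 5-point expectation and a non-inferiority aim depends on how that sentence is read, and the fault is a mismatch of formula and test, not a slip in calculation. The risk of misreading is a reason to add a sentence, not a quotation from the plan.

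None of it restores the 80%. For that, the SD would have to fall from 8 to about 4.8, a cut in variance of about 64% (1 − 4.79²/8²). The SD of 8 is already stated for change scores, and the decision rule is on the difference in change scores. Nor is this a detail that an article leaves to a fuller document: the calculation and the decision rule are both printed, and they do not match.

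**Conclusion.** The concern holds. The stated 80% power belongs to a two-sided test of a 5-point difference, which is not the primary test. Under the protocol's own SD, sample size, margin and 95% interval, non-inferiority power is about 39% if the modes are truly equal, and the expected half-width of the interval (3.51) exceeds the margin (3). Reaching 80% would take 112 analysed per arm, 2.8 times the planned 40 (112/40).

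The exact figure rests on a true difference of 0 and an SD of 8. The conclusion is less sensitive: power stays well below 80% with all 94 recruits analysed, with a one-sided 0.05 test, with an SD of 6, or with online truly 1 point better. It reaches about 80% only if online is truly about 2 points better, or the SD is about 4.8. This must be corrected, because the power claimed for the primary hypothesis is about twice what the design provides.

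**What to change.** In the sample-size section {14}:
- Replace the calculation with the non-inferiority formula on the 3-point margin, with the assumed true difference stated.
- Report that 40 analysed per arm gives about 39% power at SD 8 and true difference 0, with an expected 95% half-width of about 3.5 points.
- Remove the 5-point expected difference as the basis for the sample.
- Say whether 80 or 94 is the enrolment target, so that it agrees with Recruitment {15}.

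In Statistical methods {20a}, state before unblinding that an interval containing 3 is inconclusive and is not evidence that online delivery is inferior. Present the trial as estimating the online minus in-person difference. Leave the margin at 3; it should not be widened to suit the sample.

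The cost is rewording and a less favourable stated power, with no extra patients. The estimation framing also calls for matching edits in the hypotheses, Trial design {8}, the comparator section {6b} and the interim analyses {21b}. Enlarging the trial is the alternative, but 264 recruits at the planned 8 to 10 a month would take about 26 to 33 months (264/10 to 264/8), against a recruitment window of April 2025 to the end of February 2026.

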### Eligibility criteria {10}

Each consecutive client in the selected centers will undergo Structured Diagnostic Interview for Screening DSM-5 (TR) Disorders [63] for an initial MDD diagnosis. Additionally, patients will be assessed for eligibility based on the below given inclusion criteria:i.The clients should exhibit symptoms of MDD.ii.Male and female clients will be selected equally.iii.Clients between the ages of 20 and 50 will be selected. It was because this study is not on children or older clients.iv.Clients should preferably be "treatment-naive," meaning they have no recent history of any psychotherapy or medication. This ensures that the adapted EMDR therapy can be implemented effectively without interference from previous therapies and to avoid confounding effects.v.There must be no significant neuropsychological or cognitive disorders among patients.vi.MDD with comorbid Anxiety is permitted in this study; however, clients should not have any other comorbid symptoms.

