## Assignment of interventions: allocation

### Sequence generation {16a}

A covariate-adaptive randomization (minimization) approach with a random element will be employed to allocate participants in a 1:1 ratio to the intervention arms. This method is specifically designed to maintain balance across key prognostic variables in trials with moderate sample sizes and multiple baseline covariates, while preserving allocation unpredictability [64, 65]. Randomization will be implemented centrally using a pre-specified Python-based algorithm, executed by an independent research assistant following completion of baseline assessments. The algorithm evaluates imbalance across predefined covariates—including study site, gender, baseline depression severity, and psychiatric comorbidity—and assigns participants to the treatment arm that minimizes overall imbalance, with a probabilistic element (i.e., less than 100% deterministic assignment) to reduce predictability. This approach avoids the limitations of excessive stratification and fixed block randomization while ensuring transparent, reproducible, and auditable allocation. A detailed description of the randomization algorithm, operational procedures, and audit trail is provided in Supplementary File A, and Fig. 3 presents the CONSORT flow diagram illustrating participant allocation.

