### Concealment mechanism {16b}

An independent research assistant will generate the randomization sequence using covariate-adaptive algorithms accounting for age, gender, depression severity, and comorbidity, with a 1:1 allocation to treatment groups. The randomization sequence will be securely stored in password-protected documents accessible exclusively to the principal investigator and the designated research assistant, with access logs maintained for auditing purposes. Allocation concealment will be ensured until assignment, and outcome assessors and data analysts will remain blind to group allocation throughout the trial. Due to the nature of the intervention, blinding of clients to treatment delivery mode (online vs. in-person EMDR) is not feasible. Group assignment will be implemented electronically via either OpenClinica (https://www.openclinica.com) or Sealed Envelope (https://www.sealedenvelope.com) platforms, which reveal only the immediate next assignment following completion of baseline assessments. This dual protection system—combining restricted access to master randomization lists with electronic allocation masking—ensures compliance with CONSORT and SPIRIT standards for allocation concealment.

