### Relevant concomitant care permitted or prohibited during the trial {11d}

As specified in the eligibility criteria, patients should preferably be treatment-naive (with no recent psychotherapy or medication use) to minimize confounding effects. However, exceptions will be made for cases where patients experience severe dissociation, derealization, or emotional dysregulation that compromises therapy adherence. In such instances, concomitant antidepressant medications may be prescribed by a psychiatrist and will be carefully documented (including dosage and frequency). For patients already taking antidepressants at baseline, these medications will not be discontinued to avoid destabilization. The primary objective in these cases will be to establish emotional stability to enable continued participation in the study protocol. Throughout the trial, patients will receive psychoeducation emphasizing the importance of not initiating any new psychological interventions. These measures are designed to balance scientific rigor with ethical clinical care while minimizing confounding variables.

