Furthermore, following the procedures outlined by George and Mallery [84], General Linear Model Repeated Measures (GLM-RM) analyses will be conducted to examine longitudinal changes in major depressive disorder (MDD) and comorbid anxiety symptoms across assessment time points. The GLM-RM framework will be used to test the main effect of time, the main effect of treatment group (face-to-face vs. online EMDR), and the group × time interaction, which represents differential change over time between treatment modalities. Where significant effects are observed, planned post-hoc comparisons with Bonferroni correction [85] will be performed to examine changes in symptom severity between baseline (T01) and end of treatment (T04).

Finally, to account for repeated observations nested within individuals and to examine individual variability in symptom trajectories, hierarchical linear modeling (HLM) using maximum likelihood estimation will be employed, following the analytic guidelines described by Garson [86]. In these models, Level-1 will represent repeated symptom measurements over time, and Level-2 will represent individual participants. Time will be operationalized as the number of treatment sessions from baseline to follow-up and coded sequentially (e.g., 1, 2, 3, 4, 5…). Predictor variables will be entered as covariates and examined as fixed effects (representing average effects across participants) and, where appropriate, as random effects (representing individual variability in intercepts and slopes). Given the frequent co-occurrence of depressive and anxiety symptoms [87], reciprocal associations between depression and anxiety over time will be examined using HLM-based reciprocal association methodology [77, 80] and a 1–1–1 multilevel mediation modeling approach [88, 89].

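### Treatment-naive entry is claimed to rule out confounding, but it is only a preference and clients on antidepressants are admitted; this mainly weakens the claim of symptom reduction over time (hypothesis iii)

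*Protocol article*

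**What the plan says.** Eligibility criteria {10}, criterion iv, reads: "Clients should preferably be 'treatment-naive,' meaning they have no recent history of any psychotherapy or medication". The sentence that follows states the purpose: "This ensures that the adapted EMDR therapy can be implemented effectively without interference from previous therapies and to avoid confounding effects". How recent is too recent is not defined.

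Relevant concomitant care {11d} repeats that treatment-naive status is preferred and then provides for clients who are not: "For patients already taking antidepressants at baseline, these medications will not be discontinued to avoid destabilization". It also lets a psychiatrist start antidepressants during the trial in named circumstances, with dosage and frequency documented.

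Clients selection and sample size {14} and Recruitment {15} describe consecutive rolling enrolment, in which each client who meets the criteria is taken until the target is reached.

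Two lists of allocation factors are given. Sequence generation {16a} has "including study site, gender, baseline depression severity, and psychiatric comorbidity"; Concealment mechanism {16b} has "covariate-adaptive algorithms accounting for age, gender, depression severity, and comorbidity, with a 1:1 allocation to treatment groups". Neither names medication.

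The non-inferiority comparison in Statistical methods {20a} is a difference in HAM-D-17 change scores from baseline to end of treatment, with no covariate named. For the hierarchical models the same section says only "Predictor variables will be entered as covariates and examined as fixed effects". The subgroups in Additional analyses {20b} are age, baseline severity and trauma history. The per-protocol definition in {20c} uses session completion and fidelity.

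**The concern.** The protocol asserts a property that its own rules do not deliver. A preference cannot ensure a treatment-naive sample. Consecutive enrolment offers no step at which a treatment-naive client is chosen over a medicated one. Section {11d} expects medicated clients at baseline. Sites may also read the preference differently, one as an exclusion and another as no restriction.

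The property matters most for hypothesis iii, which holds that the adapted therapy will bring about a significant reduction in depressive symptoms over time in both modes. Both arms receive the therapy and there is no untreated arm, so randomisation does not separate the effect of the therapy from that of an antidepressant taken alongside it. Treatment-naive entry is the one safeguard the protocol states against that explanation. Without it, part of the change from baseline could belong to medication, and no section shown says how the analysis would tell.

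**Working it through.** **The plan's own figures.** Section {14}: n = (1.96 + 0.84)² × (2 × 8²) / 5² = 7.84 × 128 / 25 = 40.14, stated as 40 per arm. With 15% dropout, 80 / 0.85 = 94.1, stated as 94. Both reproduce and are unaffected by this point. They supply two inputs: 40 analysed per arm and an SD of 8 for change scores. The margin of 3 points comes from {20a}.

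**Inputs the documents do not give (assumptions).** The share p of clients on antidepressants at entry is taken as 20–40%. The contribution e of the drug to HAM-D-17 change over treatment is taken as 2–4 points. Lower prevalences of 5–10% are also shown.

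**Step 1: within-arm change (hypothesis iii).** If drug and therapy effects add, the average change in an arm contains p × e points due to medication.
- p = 0.2, e = 2: 0.4 points
- p = 0.4, e = 4: 1.6 points
- p = 0.05, e = 2: 0.1 points
- p = 0.10, e = 4: 0.4 points

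Nothing in the design removes this amount from the change over time.

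**Step 2: difference between arms (non-inferiority).** Under the same additive model the expected medication share p × e is equal in both randomised arms, so it cancels from online minus in-person. What remains is chance imbalance, which is part of the variance of the change scores.
- Standard error: 8 × √(2/40) = 1.79. The 95% half-width is 1.96 × 1.79 = 3.51.
- Variance due to medication: p(1 − p)e² = 0.16 × 4 = 0.64 at the low end and 0.24 × 16 = 3.84 at the high end.
- Share of the total variance of 64: 1% and 6%.
- Reduction in the standard error from adjusting: 1 − √0.99 = 0.5% and 1 − √0.94 = 3.0%. The half-width falls from 3.51 to 3.49 or 3.40.
- At 5–10% medicated: 0.0475 × 4 = 0.19 to 0.09 × 16 = 1.44, or 0.3–2.3% of the variance. The reduction in the standard error is about 0.15–1.1%.

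**Step 3: size of a chance imbalance.** The SD of the difference in medicated proportions is √(2p(1 − p)/40), which is 0.089 at p = 0.2 and 0.110 at p = 0.4 under simple 1:1 allocation. An imbalance of 1.96 SD would move the difference by 1.96 × 0.089 × 2 = 0.35 to 1.96 × 0.110 × 4 = 0.86 points. This is an extreme of a random error with mean zero that the confidence interval already covers.

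**The case against.** The two sections agree on the rule: {11d} refers back to the eligibility criteria and repeats the preference, so only the assurance attached to it is wrong. That is largely fair, but the assurance is the stated reason for the criterion, and a preference that consecutive enrolment cannot apply still leaves sites without one rule.

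The absence of medication from the factor lists proves less than it seems. The list in {16a} is introduced as a partial one and points to a supplementary file that is not shown. The hierarchical models allow covariates without naming them, and a statistical analysis plan may name them. This stands: the most that can be said is that medication is not named in the text at hand, not that it is left unbalanced and unadjusted. Site is also a factor in {16a}, although not in {16b}, which would help balance differences between sites in how the preference is applied.

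The assumed prevalence of 20–40% may be high for a trial that prefers treatment-naive clients, and clients who still score 20 or more at entry despite medication may gain little more from it. Both are possible. The protocol gives no figure for either, and this is why ranges are shown.

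A reader might infer that shared improvement on medication biases the trial towards non-inferiority. The documents do not support this. With additive effects the shared part cancels (step 2). Masking a true difference would need a floor effect on the scale or an interaction between medication and delivery mode, and the protocol gives no basis for assuming either. A reader might also set the 0.35–0.86 points of step 3 against the 3-point margin, as 12–29% of it, and call that bias. It is random error already within the interval.

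**Conclusion.** The stated property, treatment-naive entry that rules out confounding, is not one this design has. That follows from the text alone and needs no assumption.

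The main consequence is for hypothesis iii. Concurrent antidepressants could explain part of the reduction over time, on average 0.4–1.6 points under the assumptions of 20–40% medicated and a 2–4 point drug contribution, and 0.1–0.4 points at 5–10% medicated.

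For the non-inferiority contrast the effect is small. Randomisation prevents systematic confounding, and naming medication as a covariate would gain about 0.5–3% of the standard error on the 20–40% assumptions. The case for adjusting there is modest precision and credibility, not removal of a bias. The point deserves correction because the change is cheap and the claim about symptom reduction depends on it; it does not undermine the randomised comparison.

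**What to change.** 1. Reconcile Eligibility criteria {10} and Relevant concomitant care {11d} into one entry rule on current and recent treatment, with the time window stated, applied at all sites. Which rule is right is for the investigators; this point takes no position on it.
2. If medicated clients remain eligible, delete the statement that the criterion ensures freedom from interference and avoids confounding.
3. Record antidepressant use at baseline (yes/no) for every client, including those already enrolled. Name it as a covariate in the primary and longitudinal models. In the longitudinal models add its interaction with time, because a main effect alone adjusts the level of symptoms and not their change.
4. Add a sensitivity analysis of the non-inferiority contrast and of the within-arm change, restricted to clients unmedicated at entry. Because the restriction uses a baseline characteristic, the arms remain comparable by randomisation.

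Adding medication as a minimisation factor would now achieve little, since Trial status expects recruitment to end in February 2026.

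The cost is some wording, one binary covariate and its time interaction, and lower precision in the restricted analysis. If 20–40% are removed, 32 to 24 per arm remain, and the half-width rises from 3.51 to 1.96 × 8 × √(2/32) = 3.92 or 1.96 × 8 × √(2/24) = 4.53 points. That analysis can show whether the estimates shift, but it should not be expected to establish non-inferiority by itself. Nor does it remove other explanations of change over time that the lack of an untreated arm leaves open.
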